### Objectives

The primary objectives include:
To evaluate the effectiveness of the sensitization/education of social groups about MRDT (social group intervention) in increasing the demand (use and/or request) for MRDT compared to usual practice (control)To evaluate the effectiveness of the sensitization/education of social groups about MRDT and training of providers in health communication about MRDT with patients/caregivers (social group/provider intervention) in increasing the demand for MRDT compared to usual practice (control)To evaluate the effectiveness of the social group/provider intervention in increasing the demand for MRDT compared to the social group intervention

The secondary objectives include:
To evaluate the effect of the interventions on the care-seeking practices and pattern of anti-malarial drug use among community membersTo assess the effect of the interventions on the knowledge and opinions of respondent female heads of households (female primary care givers) about malaria and malaria diagnosisTo evaluate the effect of the interventions on the number of patients with suspected malaria visiting the public primary health facilitiesTo assess the effect of the interventions on the knowledge and opinions of healthcare providers and their practice of health communication about malaria and malaria diagnosisTo evaluate the cost-effectiveness of the interventionsTo assess the level of demand (use and/or request) for MRDT, care-seeking practices and pattern of anti-malarial drug use among community members with fever or malaria-like illnessTo assess the level of knowledge and opinions of female heads of households (female primary care givers) and of healthcare providers about malaria and malaria diagnosisTo ascertain the factors that influence the demand for MRDT among community members

### Hypotheses

The social group intervention is more effective (and more cost-effective) in increasing the demand (use and/or request) for MRDT compared to control.The social group/provider intervention is more effective (and more cost-effective) in increasing the demand for MRDT compared to control and compared to social group intervention alone.

The social group intervention is expected to enhance the knowledge and opinions of community members about malaria and malaria diagnosis and their preference for MRDT. This will lead to a moderate increase in their demand for MRDT compared to community members in the control arm. The social groups/provider intervention is expected (to a greater extent) to enhance the knowledge and opinions of the community members and their preference for MRDT. This intervention will also enhance the knowledge and opinions of healthcare providers about malaria and malaria diagnosis and their preference for MRDT. These will lead to a large increase in the demand for MRDT among community members compared to community members in the control arm. The summary of the study’s logical framework is shown in Fig. 2.

**Fig. 2 Fig2:**
[figure not shown]
Summary of the study’s logical framework

### Outcome measures

#### Primary outcome

The primary outcome is the proportion of children under 5 years of age with fever or malaria-like illness, in the 2 weeks preceding a population-based household survey, who received MRDTThe co-primary outcome is the proportion of children ages 5 years and above and adults (excluding pregnant women) with fever or malaria-like illness, in the 2 weeks preceding a population-based household survey, who received MRDT

#### Secondary outcomes

The main secondary outcomes at the community level include:
The proportion of these children under 5 years of age, who received MRDT, whose caregivers requested the MRDTThe proportion of these children ages 5 years and above and adults, who received MRDT, who requested or whose caregivers requested the MRDTThe proportion of children under 5 years of age with fever or malaria-like illness, in the 2 weeks preceding a population-based household survey, whose caregivers sought care with a provider, those that sought care the same or next day and among those for whom care was sought, the type of provider with whom care was soughtThe proportion of these children under 5 years of age who took any anti-malarial drug and who took ACTs.The proportion of children ages 5 years and above and adults (excluding pregnant women) with fever or malaria-like illness, in the 2 weeks preceding a population-based household survey, who sought care with a provider, those who sought care the same or next day and among those who sought care, the type of provider with whom care was soughtThe proportion of these children and adults who took any anti-malarial drug and who took ACTs.The proportion of respondent female heads of households (female primary care givers) with good knowledge and opinion about malaria and malaria diagnosis.

The secondary outcomes at the provider level include:
The number of patients with suspected malaria visiting the public primary health facilities (monthly) as identified in the patients’ registerThe proportion of providers with good knowledge and opinion and good health communication about malaria and malaria diagnosis.

Cost outcomes include the total cost of the social group and social group/provider interventions, average cost per provider who participated in the provider training and average cost per social group member who participated in the social group sensitization/education.

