The moderator will then highlight and discuss the key actions that the participants should exercise and promote as individuals, social group members, opinion leaders, parents, heads of households, family members, friends and relatives, neighbours, etc. These actions include recognizing the symptoms of malaria especially in children under 5 years of age, promptly seeking care with providers that carry out MRDT (preferably in the public primary health facilities) and requesting the “simple test” for malaria (MRDT), receiving the test, asking for the result, and receiving treatment for malaria (with ACTs) only when the test is positive, making sure children under 5 years of age receive treatment within 24 hours of on-set of fever and acquiring and giving the appropriate ACTs at the correct dose for the correct number of days. The moderator will then make closing remarks and thank the participants for their time.

The second and third episodes will take a similar format as the first but will focus more on re-emphasizing the key facts and actions to practice and promote so as to reinforce participants’ knowledge and attitudes. The participants will be encouraged to share their experiences in the preceding 4 weeks for discussion and clarification. Visits to the social groups will end with the third episode of group discussion. However, group members will be able to contact the investigators on their cell phones if they still require clarification on malaria and MRDT during the subsequent months.

Other supportive interventions will include reminder text messages sent at least weekly to social group members that have cell phones, regular phone calls to social group heads (to urge them to remind and encourage the group members during meeting sessions) and regular visits by a provider (PMV or public) to the scheduled meetings of each social group for provision of MRDT services and ACTs for positive results.

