The facilitators will then introduce the participants to a health communication guide on how to effectively educate their clients during the discharge of their duties. They will be educated on how to use the guide in communicating with all categories of clients including those that requested MRDT or freely accepted providers’ suggestion of a test or initially declined to receive the test. The participants will then apply the guide in another round of simulation exercise. Participants will then complete an assessment form on which they will rate the training process and logistics, state what they believed or knew previously that has now been corroborated, what they believed or knew previously that has now been contradicted, what they just learnt for the first time and any additional key actions that can be taken or promoted to increase the use of MRDT and adherence to test results. The participants will be encouraged to use the health communication guide to effectively communicate with their clients (suspected malaria cases) about MRDT at the course of their regular duties. A facilitator will then give the closing remark and implore the participants to develop their communication skills by putting it to practice immediately.

The training workshop will be followed by a twice weekly reminder text message and a monthly visit to each of the participating providers for supportive supervision (on-the-job training) and monitoring throughout the rest of the 3-month intervention period. Each support visit will be aimed at assessing providers’ performance, exploring their experiences in the previous weeks and addressing their challenges in health communication with their clients. The on-the-job training will make the intervention more pragmatic and will optimize adherence to the trial intervention. The healthcare provider’s intervention will be discontinued whenever requested by the respective provider.

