#### Data analysis

Data will be double-entered using Microsoft Excel 2007 (Microsoft Inc., Redmond, WA, USA) and analysed using Stata version 15 (Stata Corp, College Station, TX, USA). Since the number of subjects/household members on whom data will be collected is expected to vary across clusters (due to the method employed for the household survey), the “sample” command will be used to randomly select an equal number of subjects across clusters for analysis. All analyses will be on an intention-to-treat basis.

The effect of the interventions on the primary outcome will be analysed using cluster-level methods for stratified, cluster-randomized trials with a small number of clusters per treatment arm [39, 40]. Point estimates of the intervention effects (risk difference) in each intervention arm compared to control and in both of the intervention arms compared to each other will be computed from the unweighted mean of cluster-level summaries (proportions) of the outcome measures in each study arm. But since the cluster size (sample size across clusters) is constant, this point estimate will be identical to that obtained from the weighted average of individual values [39, 40]. Also, since the number of clusters across strata is constant, the estimated risk difference will be identical to the weighted average of stratum-specific risk difference.

An overall test of the null hypothesis of no difference between any of the study arms will be conducted in a two-way analysis of variance (ANOVA) of the cluster-level proportion on stratum and treatment arm. This overall test is to guide the interpretation of any subsequent significant findings in pair-wise comparisons. If the distribution of the cluster summaries in each study arm is markedly skewed, logarithmic transformation may be considered before analysis. Before conducting pair-wise significance testing and computing a confidence interval, an estimate of the within-stratum between-cluster variance will be obtained as the residual mean square from two-way ANOVA of the cluster-level proportions on stratum and treatment arm, including interaction terms. The within-stratum between-cluster variance will then be used in a stratified *t* test to test the null hypotheses of no difference in the primary outcome between each intervention arm and the control and between the two intervention arms. It will also be used in computing the corresponding 95% confidence interval of each risk difference.

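### Both MRDT request outcomes are counted only among people who were tested, so their comparison between arms is not protected by randomisation and can move against requests per fever

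*Protocol article*

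**What the plan says.** All references are to the protocol article.

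- **Objectives.** The first primary objective is to evaluate the social group intervention "in increasing the demand (use and/or request) for MRDT compared to usual practice". The other two primary objectives concern the same demand.
- **Primary outcome.** "The primary outcome is the proportion of children under 5 years of age with fever or malaria-like illness" who received the test within the two-week recall window. The co-primary outcome is the same measure in older children and adults. Both use all febrile subjects as denominator.
- **Secondary outcomes.** Request appears only in two outcomes, one per age group. For the under-fives it is "The proportion of these children under 5 years of age, who received MRDT, whose caregivers requested" the test. The version for older children and adults is also restricted to those who received MRDT.
- **Sensitization and education of social groups.** The actions taught include "requesting the “simple test” for malaria (MRDT), receiving the test, asking for the result".
- **Training of healthcare providers** (social group/provider arm only). Providers learn to communicate with "all categories of clients including those that requested MRDT or freely accepted" a suggestion of the test from the provider. The plan therefore recognises that a test can happen without a request.
- **Sample size.** Receipt is assumed to be 11%, 31% and 51% in the three arms, with 50 subjects per cluster and 300 per arm after inflation.
- **Data analysis.** The cluster-level methods of the primary outcome are also applied to the secondary outcomes to estimate intervention effects.

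**The concern.** The denominator of each request outcome is the set of people who received MRDT. That set forms after randomisation and is the numerator of the primary or co-primary outcome, which the interventions are designed to enlarge. Three things follow.

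1. The tested people in one arm need not resemble the tested people in another. A difference in request share can come from who was tested rather than from any change in asking.
2. Someone who asked for the test and did not get it is in neither the numerator nor the denominator. Under the primary outcome that person counts simply as untested.
3. A test that follows a provider's suggestion adds to the denominator without adding a request. The share can therefore drop while more febrile people ask.

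At stake is the reading of the request part of demand. This matters most for the two intervention arms, where one has provider training and the other does not, and that is the comparison that set the sample size.

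**Working it through.** **Inputs from the protocol (Sample size).** Receipt rates T are 0.11, 0.31 and 0.51 for febrile under-fives. Coefficient of variation is k = 0.16, with m = 40 per cluster for the calculation and 50 after inflation, 6 clusters per arm, 80% power and 5% type I error (two-sided assumed). The protocol gives no rates for the older group and no request shares for anyone. Every request share and unmet-request count below is an assumption for illustration.

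**Step 1: reproduce the plan's figure, to confirm the receipt rates it rests on.**
c = 1 + (1.96 + 0.84)² × [p0(1−p0)/m + p1(1−p1)/m + k²(p0² + p1²)] / (p0 − p1)²

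- 31% vs 51%: bracket = 0.00535 + 0.00625 + 0.00912 = 0.0207, and c = 5.06, rounded up to 6.
- 11% vs 31%: c = 3.07, rounded up to 4.
- The larger is 6, as stated. Inflation: 40/0.80 = 50, and 18 × 50 = 900.

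**Step 2: denominators of the request outcome.** Expected number tested = 300 × T.

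| Arm | All febrile | Expected tested | Per cluster of 50 |
|---|---|---|---|
| Control | 300 | 33 | 5.5 |
| Social group | 300 | 93 | 15.5 |
| Social group/provider | 300 | 153 | 25.5 |

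**Step 3: when the share and the requests move in opposite directions.** Let r be the share of tested people who asked. Requests that led to a test, per fever, are T × r. From arm 0 to arm 1 these rise while r falls when T0/T1 < r1/r0 < 1. The lower limits are:

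- control to social group: 0.11/0.31 = 0.35
- social group to social group/provider: 0.31/0.51 = 0.61
- control to social group/provider: 0.11/0.51 = 0.22

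**Step 4: a worked case for the two intervention arms (assumed counts per 300 febrile).**

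| | Tested | Tested on request | Asked, not tested | Planned outcome | Met requests, all fevers | All requests, all fevers |
|---|---|---|---|---|---|---|
| Social group | 93 | 60 | 10 | 60/93 = 64.5% | 60/300 = 20.0% | 70/300 = 23.3% |
| Social group/provider | 153 | 66 | 12 | 66/153 = 43.1% | 66/300 = 22.0% | 78/300 = 26.0% |

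The planned outcome falls by 21.4 points, while requests per fever rise by 2.7 points. The ratio of shares is 43.1/64.5 = 0.67, inside the range 0.61 to 1.

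**Step 5: selection alone.** Suppose half of the 31% already tested had asked, nobody changes their asking, and a further 20% are tested because providers offer. If a fraction q of these had asked, the planned outcome is (0.31 × 0.50 + 0.20 × q)/0.51.

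- q = 0: 0.155/0.51 = 30%
- q = 0.30: 0.215/0.51 = 42%
- q = 0.50: 0.255/0.51 = 50%

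The share stays at 50% only if the newly tested had asked at the same rate as those already tested.

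**The case against.** **What stands on the other side.** These are secondary outcomes, and both primary outcomes use all fevers. Receipt alone already satisfies the use part of demand. The share among the tested is a legitimate description of how tests came about. The list of main secondary outcomes is not worded as closed. The household questionnaire is said to cover demand for MRDT among fever cases, so it may already ask untested subjects about requests. None of this repairs the two outcomes as defined: they would discard those answers and would still be compared between arms.

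**Stronger readings that the protocol does not support.**

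- *The share will fall in the social group/provider arm.* That arm also receives the full social group intervention, which teaches requesting. The protocol mentions clients who accept a provider's suggestion but does not say that training aims at more unprompted offers. A fall requires receipt to grow faster than met requests.
- *The trial cannot say whether requests rose.* Within each cluster, the proportion tested times the share of tested who asked gives met requests over all fevers. Only unmet requests are missing from the listed outcomes, and their size is unknown.
- *The plan contradicts its own analysis principle.* "All analyses will be on an intention-to-treat basis" can be read as analysing clusters in the arm to which they were allocated, which is possible for a conditional outcome. The fault is selection after randomisation.
- *The all-fever denominator is far more precise.* Its standard error is smaller in percentage points only because the percentage is smaller. With 11% tested and a 30% request share, the all-fever proportion is 0.033, its binomial standard error on 300 is √(0.033 × 0.967/300) = 0.0103, and the relative error is 31%. A binomial simulation of the conditional arm mean gives 8.9 points on 30%, or about 30%. The case rests on validity, not precision.
- *The unweighted and individual-weighted means must agree here too.* The protocol says this of the primary outcome with constant cluster size and does not extend it to these outcomes, so nothing stated is wrong.
- *The provider-type outcome has the same fault.* The type of provider is reported "among those for whom care was sought, the type of provider with whom care" was sought, but care-seeking over all fevers is listed beside it. This is at most a minor reporting point.

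**Conclusion.** The concern holds in limited form. Both request outcomes condition on receipt of MRDT, an event after randomisation that the plan itself expects to differ by arm (11%, 31%, 51%; about 33, 93 and 153 of 300), and they are compared between arms as effects. The comparison is therefore not protected by randomisation and leaves out unmet requests. For social group versus social group/provider, it can point the opposite way to met requests per fever whenever the ratio of shares is between 0.61 and 1.

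The receipt rates are the protocol's, for under-fives. All request shares are assumed, so the size and direction of any distortion cannot be predicted. The primary and co-primary outcomes are unaffected. The denominator is written into the outcome definition, so it is not a detail left to an unseen analysis plan.

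**What to change.** For each age group:

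1. Replace the request outcome with the proportion of all subjects with fever or malaria-like illness for whom MRDT was requested (by the caregiver, or in the older group by the subject or caregiver), whether or not it was received. Use the primary outcome's denominator.
2. Add the proportion of the same subjects for whom MRDT was received and/or requested, to match the objectives.
3. Keep the share of tested subjects who had asked as a description of how tests arose, without a test or interval for the difference between arms.

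Confirm that the questionnaire puts the request question to untested subjects. If it did not in a completed survey round, report at least requested-and-received over all fevers, computed cluster by cluster from counts already collected, and state that unmet requests are not captured.

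Cost: new outcome wording, possibly one routing change in the questionnaire, and smaller percentages in the report. No extra subjects are needed. The routing change may come too late for the surveys: recruitment was expected to end by 29 June 2019 and the article appeared on 10 October 2019. The requested-and-received fallback needs no new data.

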### Measurement of study outcomes

#### Population-based household survey

The survey questionnaire was adopted from the 2015 NMIS [15] woman’s questionnaire and was modified to collect data on both the primary outcome and community-level secondary outcomes. The questionnaire will be pre-tested in non-participating clusters before the survey. Interviewers will be recruited and trained over a 1-week period to administer the questionnaire. The training of the interviewers will include a detailed review and explanation of the questionnaire items, interview techniques, how to provide information to household respondents about the survey, how to obtain consent, the translation of key words in the questionnaire to local language and how to administer the questionnaire. The baseline survey will be carried out before the intervention (see Fig. 1) to collect data for the assessment of the level of demand (use and/or request) for MRDT among community members with fever or malaria-like illness in Ebonyi state. A section of the questionnaire will collect data on the determinants of the demand for MRDT. The end-of-study survey will be carried out 3 months after the end of the intervention (see Fig. 1) to collect data for the evaluation of the effects of the interventions on the demand for MRDT among community members.

The interviewers will be accompanied by research supervisors at the start of the baseline survey for monitoring and supportive supervision. This will be followed by a visit at least once weekly for monitoring and supportive supervision. The household survey questionnaire is designed to collect data about the following items from the respondent female head of household (the mother of the house or female primary care giver):
Basic socio-demographic characteristics (of the respondent and of eligible household members reported to have had fever/malaria-like illness in the preceding 2 weeks)Fever/malaria-like illness management including care seeking and demand for MRDTThe respondent’s knowledge and opinions about malaria and malaria diagnosisThe determinants of the demand for MRDT

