### Participants and participant timeline

#### Participants

##### Clusters

Clusters eligible to participate in the study include villages/settlements (a community) that have at least one eligible public primary healthcare facility and one eligible PMV (see below) and are easily accessible (close to a motorable road) even in the rainy season. Clusters either participating in or that have participated in any similar interventions within the preceding year will be excluded from participating in the study. Clusters that are too close (less than 15 km apart) and are not separated by a buffer area or natural barrier, and urban clusters (in cities/towns) will be excluded from participating in the study to minimize contamination between clusters within strata [39, 40]. Non-consenting clusters will also be excluded from participating in the study.

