##### Primary health facilities and individual healthcare providers

Eligible public primary health facilities are those providing MRDT services, maternal and child healthcare services including immunization, attending to at least an average of four patients with fever (or suspected malaria) per day and having at least two staff that are at least junior community health extension workers (JCHEWs). Individual public healthcare providers involved in the diagnosis (and treatment) of malaria in these facilities are eligible. Eligible PMVs are those with basic training in MRDT services and either currently offering or having previously offered MRDT services. Non-consenting health facilities and individual providers will be excluded from the study.

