#### Sample size

After comparing the required sample size for each of the primary objectives, the largest sample size will be used. This is based on the primary objective to evaluate the effectiveness of the social group/provider intervention compared to the social group intervention in increasing the demand for MRDT in the communities. The sample size is estimated using the methods recommended for a stratified, cluster-randomized trial [39, 40] and will be based on the primary outcome of the proportion of children under 5 years of age with fever or malaria-like illness, in the 2 weeks preceding a population-based household survey, who received MRDT. A plausible estimate of the primary outcome of 11% in the control arm will be used, based on the reported value for the south-east zone (that includes Ebonyi state) in the NMIS 2015 [15].

Assuming a coefficient of variation between clusters within strata of 0.16, a sample size per cluster of 40 eligible children under 5 years of age and 80% power at 5% probability of type I error, the trial will require 6 clusters per arm to detect a difference of 20% in the primary outcome between the control arm and the social group arm (an increase from 11% to 31%) and a difference of 20% between the social group arm and the social group/provider arm (an increase from 31% to 51%). A sample size per cluster (cluster size) of 40 subjects with 6 clusters per arm gives a total cluster number of 18, with 240 subjects per arm and a total sample size of 720 subjects. The sample size per cluster (of 40) will be increased by 20% (to 50) to compensate for any probable invalid records and other field eventualities. This gives a final cluster size of 50 subjects with 300 subjects per arm and a total sample size of 900 subjects.

The same sample size will be used to assess the co-primary outcome of the proportion of children ages 5 years and above and adults (excluding pregnant women) with fever or malaria-like illness, in the 2 weeks preceding a population-based household survey, who received MRDT. An equal number of clusters (*n* = 6) will be allocated to each arm and to each stratum and, despite variations in population size in the clusters, an equal fixed sample size (*n* = 50 for each target population) per cluster will be used to optimize statistical efficiency [39, 40].

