Adjusted analysis based on cluster summaries will be done in a two-staged procedure. In the first stage, the covariate-adjusted residual will be obtained for each cluster using standard multiple linear regression analysis, incorporating the stratum (as a fixed effect) and all baseline cluster-level covariates of interest but excluding the intervention effect. The potential baseline covariates of interest will include cluster-level summaries of the primary outcome measure, mean scores for respondents’ knowledge and opinions (about malaria and malaria diagnosis) and other baseline variables found to differ between the study arms and which can be determinants of a particular outcome. Only cluster-level summaries of baseline covariates will be used in the adjusted analysis because baseline and follow-up data will be on different individuals, as the study employed a repeated cross-sectional design [39, 40]. The difference-residual for each cluster will be obtained as the difference between the observed outcome in each cluster and the predicted outcome in the absence of an intervention effect. The covariate-adjusted residuals will replace the cluster-level proportions in the second stage in estimating the intervention effects, which are thus adjusted for the covariates in the first stage.

The same cluster-level methods will be used to evaluate the effect of the interventions on the secondary outcomes. Comparative analysis of baseline data will be used to assess the balance between the treatment arms and potential baseline variables that will be reported include the cluster-level and individual-level summaries of the primary and secondary outcome measures, the age and sex of individual subjects, the age of the respondent female head of household, educational level, occupation, level of knowledge and opinions about malaria and malaria diagnosis and average knowledge and opinion score. Summary statistics of baseline data will be used to assess the level of demand for MRDT, care-seeking practices and pattern of anti-malarial drug use among community members with fever or malaria-like illness; the level of knowledge and opinions of the female heads of households about malaria and malaria diagnosis and the level of knowledge and opinions of healthcare providers about malaria and malaria diagnosis.

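### The baseline level of MRDT demand is described as that of Ebonyi state, but the survey covers only rural, accessible, MRDT-served communities and is not self-weighting even for them

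*Protocol article*

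**What the plan says.** **Target.** Assessing the level of MRDT demand, care-seeking and antimalarial use is one of the secondary objectives (Objectives). The section on the population-based household survey says that the baseline round provides data for the "assessment of the level of demand (use and/or request) for MRDT among community members with fever or malaria-like illness in Ebonyi state".

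**Frame.** Under Clusters, communities must "have at least one eligible public primary healthcare facility and one eligible PMV" and must be places that "are easily accessible (close to a motorable road) even in the rainy season". Also, "urban clusters (in cities/towns) will be excluded from participating in the study". The section on primary health facilities and individual healthcare providers adds: "Eligible public primary health facilities are those providing MRDT services", and these facilities must be "attending to at least an average of four patients with fever (or suspected malaria) per day". An eligible vendor (PMV) must have basic MRDT training and must offer the test now or have offered it before.

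**Sampling.** Eighteen clusters are drawn at random from the list of eligible clusters, six per stratum, with no selection by size (Sampling technique). The sample size section fixes, "despite variations in population size in the clusters, an equal fixed sample size" of 50 per target population in each cluster. Data analysis adds that surplus subjects are dropped at random so that clusters contribute equal numbers. Methods/design sets a minimum cluster of 250 households or 1,500 people and no maximum.

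**Analysis.** "Summary statistics of baseline data will be used to assess the level of demand for MRDT", together with care-seeking and antimalarial use. No weights are mentioned for these summaries.

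**The concern.** Two separate gaps lie between the stated target and what the survey can estimate.

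The first is coverage. Towns, communities without all-season road access, and communities without an MRDT-providing facility or an MRDT-trained vendor cannot enter. The presence of a testing service is a precondition for the behaviour being measured, so the frame is selected on something close to the outcome.

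The second is weighting. With equal-probability selection of clusters and a fixed take from each, a febrile person's chance of inclusion falls as the cluster gets larger. At the same fever rate, a person in a cluster of 6,000 has a quarter of the chance of a person in a cluster of 1,500. A plain summary then averages over clusters, not over people.

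At stake is how a descriptive figure is read. The Background and Discussion direct the trial's findings to state and national malaria policy, where a testing level labelled as that of the state could be taken at face value. The randomised comparisons do not depend on this.

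**Working it through.** **The plan's own figures.** 18 clusters × 50 = 900 subjects per target population, as stated. The article gives no precision for the baseline household level. It does give one for the provider survey: 42 providers per arm, 7 per cluster, ICC 0.01. With `1.96 × sqrt(p(1-p) × (1 + 6 × 0.01)/42)` this is 15.6 points at p = 0.50 and 14.3 points at p = 0.70. Both match the article, so clustering was allowed for there.

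**Coverage: can the direction be determined?** State level = u·pu + v·pv + (1-u-v)·pf. Here u and pu are the urban share and testing rate, v and pv those of rural communities that are unserved or hard to reach, and pf is the rate in the frame. Only pf has an anchor, the planning rate of 11%. The rest are assumptions: u 10 to 30%, pu 11 to 30%, v 20 to 60%, pv 3 to 11%.
- Lowest survey minus state: 0.11 - (0.3×0.30 + 0.2×0.11 + 0.5×0.11) = 0.11 - 0.167 = -5.7 points.
- Highest: 0.11 - (0.3×0.11 + 0.6×0.03 + 0.1×0.11) = 0.11 - 0.062 = +4.8 points.
- On a grid of 81 combinations, 32 are too high, 40 too low and 9 equal. These counts are not probabilities; they show that the sign is open.

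**Weighting by cluster size.** Equal-weight minus size-weighted level = `-r × CV(size) × k × p`, where r is the correlation of cluster size with testing rate. Inputs from the article: p = 0.11 and k = 0.16. Assumptions: CV(size) 0.3 to 1.0 and r from -0.5 to +0.5.
- k = 0.16: largest shift 0.5 × 1.0 × 0.16 × 0.11 = 0.0088, so about -0.9 to +0.9 points.
- k = 0.5 (assumption): 0.5 × 1.0 × 0.5 × 0.11 = 0.0275, so about -2.8 to +2.8 points.
- Illustration (assumption): equal numbers of clusters of 1,500 people at 15% and of 6,000 at 8% give 11.5% unweighted and (225 + 480)/7,500 = 9.4% per person. With the rates swapped, the figures are 11.5% and (120 + 900)/7,500 = 13.6%.

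**Weighting by stratum.** The 2016 populations of 998,473, 861,554 and 1,037,376 give shares of 34.5, 29.7 and 35.8%, against 33.3% each. If the central zone differed from the others by 10 points, the shift would be 10 × (0.3333 - 0.2974) = 0.36 points. The numbers of eligible clusters per stratum are not given, so this is only a guide.

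**Precision at 11%, 18 × 50.** ICC = k²p/(1-p); design effect = 1 + 49 × ICC.
- Clustering ignored: 1.96 × sqrt(0.0979/900) = 2.04 points.
- k = 0.16: ICC 0.0032, design effect 1.155, half-width 2.20 points, or 2.39 with t on 15 df (18 clusters minus 3 strata; t = 2.131).
- k = 0.5 (assumption): ICC 0.0309, design effect 2.51, half-width 3.24 points, or 3.52 with t.

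**The case against.** The best defence is that naming the state may only say where the study takes place. The Objectives section does not name it for this aim, and all eligibility restrictions are set out openly. That keeps the point small. It does not remove it, because the sentence gives a purpose for the survey and places no limit on the population.

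A second defence is that weights and interval methods for a descriptive summary are commonly left to a statistical analysis plan. This stands, and their absence is not the complaint. The article itself fixes both the frame and the equal allocation, and no later weighting can bring in communities that were never eligible.

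Two stronger readings are tempting, and the article supports neither.
- A reader might infer that the figure will be too high because every included community has MRDT. Leaving out unserved and remote communities probably pushes it up, but leaving out towns pushes it down if urban testing is higher. The Background says that rural febrile patients tend to go first to vendors, where testing is rare, which makes a higher urban rate plausible. All three zones are predominantly rural, which limits this offset without removing it. The size-weighting effect has no known sign either, since nothing links cluster size to testing.
- A reader might infer that the interval will be too narrow. No interval method is stated for this estimate. Clustering is allowed for in the provider survey and in the trial comparisons, so nothing shows that it would be ignored here.

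The Data analysis remark that weighted and unweighted estimates coincide when cluster sizes are equal is correct for the sampled subjects. It does not carry over to populations of unequal size.

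**Conclusion.** The point holds as a mismatch between target and frame, plus a design that is not self-weighting. The baseline figure will be the level in eligible rural, accessible, MRDT-served communities, and its distance from a state level has no determinable sign.

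Within the eligible communities, the effect of equal cluster weights is probably modest: under 1 point either way at the protocol's between-cluster variation, and up to about 2.8 points if that variation were 0.5. These sizes rest on assumed size variation and size-rate correlation, because the article gives neither. Equal allocation across strata hardly matters on the zone populations.

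The matter touches one descriptive secondary objective. It is a worthwhile, low-priority correction.

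**What to change.** 1. State the target of the descriptive objective as febrile members of eligible communities: non-urban, accessible by road, with an MRDT-providing public facility and an MRDT-trained vendor. Drop the state-level wording.
2. For the baseline levels only, report Σwᵢpᵢ / Σwᵢ over clusters, with wᵢ = (enumerated households or population of cluster i) × (eligible clusters in its stratum / 6). This assumes that two-week fever is about equally common across clusters. Do not weight by the count of febrile subjects: under Sampling technique, households that were not eligible are revisited when the quota is not met, which inflates that count in some clusters.
3. Base any interval on between-cluster variation within strata. At 11% and a coefficient of variation of 0.16 this is about ±2.4 points, against ±2.0 with clustering ignored, before any widening from the weights.
4. Leave the randomised comparisons unweighted, as planned.

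The cost is a change of wording and one weighted summary. All households in the selected clusters are to be enumerated, and the list of eligible clusters is needed for sampling anyway, so no new data are required. The price is a narrower claim and somewhat wider intervals; the widening grows with the spread of cluster sizes.
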